## **Can We Alter Risk Factors For Oesophageal Cancer With Exercise?**

### **DESIGN**

A prospective, randomised controlled trial will be implemented.

### **SUBJECTS**

#### *Inclusion Criteria*

Participants will be overweight males (BMI 25-34.99 kg/m^2)

Participants must also be Brisbane residents, aged between 18 and 70 years old with BE diagnosed via endoscopy. Furthermore, participants must be sedentary, performing less than 60 minutes of moderate intensity, structured exercise per week.

#### *Exclusion Criteria*

Potential participants with cardiac disease; uncontrolled hypertension or hypotension; diabetes; orthopaedic injuries; neurological, respiratory, haematological or inflammatory conditions; or any other serious impairment that would impede their ability to perform the exercise intervention will be excluded. Participants with a past history of cancer within 5 years will also be excluded. Participants with a BMI >35 kg/m^2 will be excluded due to safety concerns. Participants who have already commenced an exercise program or diet in the past 6 months will also be excluded as will participants who have lost or gained more than 5kg in the past 6 months.

### **RECRUITMENT**

Participants will be recruited via the following avenues:

- The gastroenterology clinic at the Royal Brisbane & Women's Hospital.
- A database of people with BE whom have previously participated in epidemiological studies at the Queensland Institute of Medical Research. A member of the research team who previously worked with these participants (A/[name]) will contact them for permission to be approached by our research team.
- Via the rooms of private gastroenterologists and the endoscopy suite at The Wesley Hospital.
- Gastroenterology department at the Princess Alexandra Hospital
- Gastroenterology department at Greenslopes Private Hospital
- Private clinics of Gastro-Intestinal Endoscopy Services (GIE)
- Gastroenterology department at The Prince Charles Hospital

## **GROUP ALLOCATION**

Participants will be allocated to one of two groups via computerised randomisation. The randomisation sequence will be protected by an electronic password. Group allocation will be concealed. Baseline measures will then be taken on all participants.

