## PRIMARY OUTCOME MEASURES

A research nurse will perform the collection of all blood samples. Fasting blood samples of 30ml will be obtained by venipuncture from the antecubital vein. Blood samples will be taken at least 24hrs since the most recent exercise session. Samples will be centrifuged, serum aliquoted for subsequent analyses and stored at -70°C. The analysis of all blood samples will be performed by blinded researchers. All blood analysis will be performed on serum.

1. Leptin and Adiponectin serum concentrations will be measured by a radioimmunoassay (RIA) from Linco Research Inc. (Australian Laboratory Services, Sydney, Australia). The intra-assay and inter-assay co-efficients of variability are less than 5%. All samples will be analysed in duplicate.
2. CRP, and IL-6, TNF-alpha serum concentrations will also be analysed using RIAs (Linco Research Inc., Australian Laboratory Services, Sydney, Australia). All samples will be analysed in duplicate. The intra-assay and inter-assay co-efficients of variability are less than 5%.
3. Glucose and insulin serum concentrations will be measured in duplicate via a fasting blood test and analysed using RIAs (Linco Research Inc., Australian Laboratory Services, Sydney, Australia). The coefficients of variation for all assays are <10%, and for insulin, <5%. Insulin resistance will be determined using the reciprocal index of homeostasis model assessment (HOMA-IR) and QUICKI index. Both measures calculate ratios of fasting insulin:glucose concentrations using different algorithms, and have been shown to be reproducible and valid measures of insulin resistance.

All primary outcome measures will be taken at the following time points:

- Once participants have enrolled, before the intervention begins (0 weeks).
- Half way through the intervention (12 weeks).
- At the conclusion of the intervention (24 weeks).

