The MSWT has been shown to strongly correlate with  $\text{VO}_2\text{max}$  during treadmill testing ( $r=0.88$ ) in patients with airflow obstruction, however we will confirm this in our population by monitoring participants with a Cortex Metamax 3 portable metabolic analyser (Cortex:biophysik, GmbH, Germany) during the test.  $\text{VO}_2\text{peak}$  will be confirmed using established physiological criteria and includes a heart rate near maximal for age, the anaerobic threshold (V-slope technique), oxygen uptake reaching a plateau with increasing work rate and a RPE of 20/20^9. The test is ceased when either:  $\text{VO}_2\text{peak}$  is obtained, the person cannot keep up with the audio tape or the person cannot continue due to breathlessness or fatigue, and requests to stop. Participants will only be monitored with the metabolic analyser during the second trial. The first trial will be used as a practice.

Given that our population is sedentary and overweight or obese, we feel maximal exertion will be reached during this test as it combines a wide range of exercise intensities from slow walking (0.50m/s) to fast running (2.37m/s). The test will be performed a second time after a 30 minute rest. A recent study of overweight, untrained middle aged males required 34 participants in each group to detect a significant improvement in  $\text{VO}_2\text{peak}$  in the exercise group.

3. Muscular Strength. To measure muscular strength, a one-repetition maximum on each resistance exercise will be taken. One-repetition maximum is the maximum weight a person can lift only one time with correct technique. It has shown to be a reliable and valid measure of strength in middle aged, untrained adults.
4. Gastro-oesophageal reflux symptom frequency and duration will be measured using a validated questionnaire. As gastro-oesophageal reflux severity is associated with obesity and increased oesophageal AC risk we are interested in the effect the exercise intervention may have on this disorder.

All secondary outcomes will be measured on enrolment (0 weeks), midpoint (12 weeks) and at the conclusion of the intervention (24 weeks).

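### Baseline is placed after randomisation, and the protocol does not say that allocation stays undisclosed until the week-0 measures are complete

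*Protocol*

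**What the plan says.** The Group Allocation section of the protocol gives a sequence. It opens with "Participants will be allocated to one of two groups via computerised randomisation", adds that the sequence is password-protected, and ends with "Group allocation will be concealed. Baseline measures will then be taken on all participants". It does not say from whom allocation is concealed, or until when.

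Two other sections date the baseline. Primary Outcome Measures has "Once participants have enrolled, before the intervention begins (0 weeks". Secondary Outcome Measures has "All secondary outcomes will be measured on enrolment (0 weeks), midpoint (12 weeks) and at the conclusion of the intervention (24 weeks". Neither places week 0 relative to randomisation.

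Blinding is stated for one activity only: "The analysis of all blood samples will be performed by blinded researchers".

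Several week-0 measures rest on effort or self-report:
- Strength: "To measure muscular strength, a one-repetition maximum on each resistance exercise will be taken". The Exercise Intervention section names seven such exercises.
- Fitness: the shuttle walk test, which may end when "the person cannot continue due to breathlessness or fatigue, and requests to stop".
- Reflux: "Gastro-oesophageal reflux symptom frequency and duration will be measured using a validated questionnaire".
- Diet: a food frequency questionnaire, dated to week 0 under Other Measures.

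**The concern.** A baseline value is a neutral starting point only if the arm cannot have influenced it. Here the stated order lets a man, and the person testing him, know the arm before the first test. Once disclosed, gym training and home stretching cannot be confused. A man may push harder or hold back on a maximal lift, stop the shuttle test sooner, or answer a symptom or diet questionnaire differently according to what he has been assigned. Any analysis that uses the baseline then takes in a difference that the intervention did not cause. For diet, the questionnaire is meant to show that the arms are comparable, so an arm-dependent answer at week 0 weakens that check.

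The second risk does not depend on how anything is measured. A man randomised and then lost before baseline belongs to the randomised set but has no data on any outcome, primary ones included. Disappointment with the assigned arm is a plausible reason to leave, so the losses could be unequal.

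**Working it through.** **Order of events.** Set side by side, the three timing statements are compatible: enrol, randomise, measure, start the intervention. The only statement that relates baseline to randomisation is the one under Group Allocation, and it puts baseline second. The outcome sections do not reverse this, and no section states that the arm is withheld through baseline.

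**How a baseline difference reaches the effect.** The documents give no figure to reproduce, so this part is algebra plus an illustration. Let *d* be the arm difference (exercise minus control, in SD units) that knowledge of the arm creates at baseline, *p* the fraction of it that persists at follow-up, and *r* the baseline-to-follow-up correlation, with equal SDs at both times.

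- Change score: bias = *pd* − *d* = −(1 − *p*)*d*.
- Baseline-adjusted: bias = *pd* − *rd* = (*p* − *r*)*d*.

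If the difference exists at baseline only (*p* = 0), the biases are −*d* and −*rd*; adjustment shrinks the bias but does not remove it. If it persists in full (*p* = 1), it cancels in the change score and leaves (1 − *r*)*d* after adjustment. The sign is not predictable: controls holding back at baseline would shrink the apparent benefit of exercise, and exercisers holding back would inflate it.

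**Illustration.** All inputs are assumptions: *p* = 0, no true effect, a two-sided 5% test, a normal approximation, and *n* = 34 per arm. The 34 is the group size the protocol quotes from a cited fitness study, not a stated target for this trial.

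- SE of the change-score contrast = √[(2/*n*) × 2(1 − *r*)].
- SE of the adjusted contrast = √[(2/*n*) × (1 − *r*²)].
- Rejection rate = Φ(|bias|/SE − 1.96) + Φ(−|bias|/SE − 1.96).

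For *d* = 0.2 and *r* = 0.5, the change-score SE is √(0.0588 × 1) = 0.243. The ratio is 0.2/0.243 = 0.82, and the rejection rate is 0.128 + 0.003 = 13.1%.

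| *d* (SD) | *r* | Change score: bias size, rejection | Adjusted: bias size, rejection |
|---|---|---|---|
| 0.1 | 0.5 | 0.10, 7.0% | 0.05, 5.7% |
| 0.1 | 0.8 | 0.10, 10.0% | 0.08, 8.5% |
| 0.2 | 0.5 | 0.20, 13.1% | 0.10, 7.6% |
| 0.2 | 0.8 | 0.20, 25.6% | 0.16, 19.6% |
| 0.3 | 0.5 | 0.30, 23.6% | 0.15, 11.0% |
| 0.3 | 0.8 | 0.30, 49.8% | 0.24, 37.8% |

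A higher correlation makes it worse: at *r* = 0.9 and *d* = 0.2 the rates are 45.4% and 39.9%. With *d* = 0 the rate stays at 5%.

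**Early loss.** The documents give no rate. With the same assumed 34 per arm, losing 1 to 3 men from one arm before baseline removes 1/34 = 2.9% to 3/34 = 8.8% of that arm from every outcome.

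**The case against.** The strongest reply is that the mechanism needs disclosure before baseline, which the protocol never states. The concealment sentence comes directly before the baseline sentence, so it can be read as withholding the arm until baseline is done. That reading is permissible and would largely remove the measurement risk. But the sentence follows one about protecting the randomisation sequence, and concealing the sequence up to assignment is at least as natural a meaning. So it is not established that men know their arm at week 0; what stands is that nothing prevents it.

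Second, all primary outcomes are fasting serum markers, or indices derived from them, assayed blind. This stands: a reader might infer that the primary comparisons are subject to the same measurement bias, and the text does not support that. Early loss is the main remaining route to them.

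Third, the fitness measure has safeguards: a practice trial, a metabolic analyser on the second trial, and physiological criteria for a true peak. These reduce the risk for predicted oxygen uptake but do not remove it, because the participant may ask to stop.

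Fourth, the full transfer of a baseline difference into a change score holds only if that difference is gone at follow-up. This is correct, and it is why *p* appears in the working.

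A reader might also infer that ineligible men would be discovered after randomisation, since BMI is both an entry criterion and a week-0 measure and glucose is assayed. The protocol does not support this. Week-0 sampling comes after enrolment, which suggests that eligibility is settled earlier. Diabetes is an exclusion with no glucose threshold attached, and serum is stored for later assay. Nor should the physical activity questionnaire be counted among the week-0 measures, because Other Measures gives it no time point.

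**Conclusion.** The point holds in a limited form. The protocol's only statement on order puts baseline after randomisation, and no text keeps the arm from participants and testers until baseline is complete. If the arm is known by then, the strength, shuttle walk, reflux and diet baselines can depend on it, and analyses that use those baselines can be biased in either direction. The exposure is mainly in secondary and other measures. Loss between randomisation and baseline could affect every outcome.

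The size is unknown. The illustrative rates rest wholly on assumed shifts, correlations and group size; they show that a modest shift would matter, not that one will occur. The point still deserves action: a later statistical plan cannot clean a baseline influenced by allocation or recover men lost before it, and prevention costs almost nothing.

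**What to change.** In Group Allocation, reverse the order: complete all week-0 measures, then randomise, then disclose the arm. In Primary Outcome Measures and Secondary Outcome Measures, state that the 0-week measures precede randomisation, so that the three sections agree.

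At the least, state that allocation is not disclosed to participants or assessors until the week-0 measures are complete. That addresses the measurement risk but still leaves men who are randomised and then lost before baseline.

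The cost is a short amendment. The measures themselves do not change and no new test is needed; only the moment of randomisation moves.

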## **EXERCISE INTERVENTION**

Participants will complete 1hr exercise sessions, at moderate intensity (60-70% of maximum heart rate), five days/week for 24 weeks. Each session will combine cardiovascular training with resistance training. The program is consistent with the American College of Sports Medicine guidelines to attain weight loss.

Participants will perform one supervised exercise session per week at the Royal Brisbane & Women's Hospital (RBWH) or The Wesley Hospital under the direction of a physiotherapist ([name]). Participants will perform the remaining four exercise sessions independently at a local gym or workplace gym as they are essentially healthy and do not require constant monitoring. Participants will document the details of their independent sessions in an exercise diary which will be reviewed by [name] on a weekly basis at the supervised session. Progression of exercises will also occur during the supervised session.

Cardiac Rehab Manager [name] has agreed to provide space in the physiotherapy gym at The Wesley hospital for the intervention to take place.

Exercise intensity will be measured via the unmodified (6-20) BORG scale. Participants will be familiarised with the scale on their initial supervised exercise session and will be instructed to maintain their rate of perceived exertion (RPE) between "fairly light" and "somewhat hard" or "steady pace". During the initial session, a pulse oximeter will be used to ensure participant's heart rates are maintained between 60-70% of maximum and correlate with the desired RPE. A variety of aerobic exercises will be prescribed to maintain participant motivation and interest such as treadmills, exercise bikes and seated rowing.

Resistance training will include: one-two sets of 8-15 repetitions performed on the major muscle groups. Free weights and machine weights will be used. Exercises will include: bench press, seated row, leg press, lunges, shoulder press, assisted chin ups and assisted dips. Resistance will be set at achieving muscular fatigue between 12-15 repetitions initially and then 8-10 repetitions after 8 weeks of training. Resistance will therefore progressively increase as the subjects enhance their strength.

## **CONTROL GROUP**

To make the groups as similar as possible the control group will attend the RBWH or The Wesley Hospital once a week to perform stretches under the instruction of [name]. The control group will also be instructed to perform the stretching program at home, four times per week. Stretching is not strenuous enough to burn significant energy to attain fat loss and will act as a sham intervention.

Participants allocated to the control group will receive a rubber mat so they can perform the stretching program comfortably at home.

The control group will be instructed not to commence a new exercise regime during the study other than the prescribed stretching program. Therefore participants will remain sedentary.

At the conclusion of the study the control group will be offered a 3 month gym membership in recognition of their involvement in the study. Offering part of the intervention to control participants at the conclusion of the study is becoming standard practice among cancer prevention clinical trials to increase retention and ultimately improve methodological quality.

## PRIMARY OUTCOME MEASURES

A research nurse will perform the collection of all blood samples. Fasting blood samples of 30ml will be obtained by venipuncture from the antecubital vein. Blood samples will be taken at least 24hrs since the most recent exercise session. Samples will be centrifuged, serum aliquoted for subsequent analyses and stored at -70°C. The analysis of all blood samples will be performed by blinded researchers. All blood analysis will be performed on serum.

1. Leptin and Adiponectin serum concentrations will be measured by a radioimmunoassay (RIA) from Linco Research Inc. (Australian Laboratory Services, Sydney, Australia). The intra-assay and inter-assay co-efficients of variability are less than 5%. All samples will be analysed in duplicate.
2. CRP, and IL-6, TNF-alpha serum concentrations will also be analysed using RIAs (Linco Research Inc., Australian Laboratory Services, Sydney, Australia). All samples will be analysed in duplicate. The intra-assay and inter-assay co-efficients of variability are less than 5%.
3. Glucose and insulin serum concentrations will be measured in duplicate via a fasting blood test and analysed using RIAs (Linco Research Inc., Australian Laboratory Services, Sydney, Australia). The coefficients of variation for all assays are <10%, and for insulin, <5%. Insulin resistance will be determined using the reciprocal index of homeostasis model assessment (HOMA-IR) and QUICKI index. Both measures calculate ratios of fasting insulin:glucose concentrations using different algorithms, and have been shown to be reproducible and valid measures of insulin resistance.

All primary outcome measures will be taken at the following time points:

- Once participants have enrolled, before the intervention begins (0 weeks).
- Half way through the intervention (12 weeks).
- At the conclusion of the intervention (24 weeks).

## SECONDARY OUTCOME MEASURES

1. Body fat will be measured using bioelectrical impedance analysis (BIA), body mass index (BMI), and the ratio of waist to hip circumference (waist:hip ratio).
  - *Bioelectrical Impedance Analysis*: BIA will be measured using a SEAC Multi-Frequency Bioelectrical Impedance Analyser (SEAC, Brisbane). BIA measures will be taken in triplicate and the results averaged. Typical coefficients of variation for within a measurement session range from 0.3 to 3%.
  - *BMI* will be also calculated ( $\text{weight}/\text{height}^2$ ) as it is a reasonable measure of global adiposity.
  - *Weight*: measured to nearest 0.1 kg in light clothing without shoes on a calibrated scale (Lindel balance scale, Samhald, Klippan Sweden) with an empty bladder.
  - *Waist Circumference*: The measuring tape is placed in a horizontal plane around the abdomen immediately above the top of the right iliac crest. The plane of the tape is parallel to the floor and the tape is snug, but does not compress the skin. The measurement is made at a normal minimal respiration (NHANES III protocol).
  - *Hip Circumference*: measured as the maximum diameter at the greater trochanter with a horizontal tape. The data will be used to calculate BMI and waist:hip ratio.

2. Cardiovascular Fitness. The Modified Shuttle Walk Test (MSWT) will be used to predict  $\text{VO}_2\text{peak}$ . The test involves walking between two markers spaced 10 metres apart at a pace set by an audio tape. The MSWT progressively gets more difficult as the speed of the tape gradually increases, eventually requiring the person to run between the markers.

A small training or learning effect has been shown between the first and second trial, therefore participants will perform the test twice with a 30minute rest in between.

The MSWT has been shown to strongly correlate with  $\text{VO}_2\text{max}$  during treadmill testing ( $r=0.88$ ) in patients with airflow obstruction, however we will confirm this in our population by monitoring participants with a Cortex Metamax 3 portable metabolic analyser (Cortex:biophysik, GmbH, Germany) during the test.  $\text{VO}_2\text{peak}$  will be confirmed using established physiological criteria and includes a heart rate near maximal for age, the anaerobic threshold (V-slope technique), oxygen uptake reaching a plateau with increasing work rate and a RPE of 20/20^9. The test is ceased when either:  $\text{VO}_2\text{peak}$  is obtained, the person cannot keep up with the audio tape or the person cannot continue due to breathlessness or fatigue, and requests to stop. Participants will only be monitored with the metabolic analyser during the second trial. The first trial will be used as a practice.

Given that our population is sedentary and overweight or obese, we feel maximal exertion will be reached during this test as it combines a wide range of exercise intensities from slow walking (0.50m/s) to fast running (2.37m/s). The test will be performed a second time after a 30 minute rest. A recent study of overweight, untrained middle aged males required 34 participants in each group to detect a significant improvement in  $\text{VO}_2\text{peak}$  in the exercise group.

3. Muscular Strength. To measure muscular strength, a one-repetition maximum on each resistance exercise will be taken. One-repetition maximum is the maximum weight a person can lift only one time with correct technique. It has shown to be a reliable and valid measure of strength in middle aged, untrained adults.
4. Gastro-oesophageal reflux symptom frequency and duration will be measured using a validated questionnaire. As gastro-oesophageal reflux severity is associated with obesity and increased oesophageal AC risk we are interested in the effect the exercise intervention may have on this disorder.

All secondary outcomes will be measured on enrolment (0 weeks), midpoint (12 weeks) and at the conclusion of the intervention (24 weeks).

